#### Hypothesis:

Early provision of AFOs ( $\pm 2$  wks after stroke) positively affects walking impairments after stroke compared to providing AFOs later on in the rehabilitation process ( $\pm 10$  wks after stroke), as the development of compensatory movements in the proximal segments of the lower limb and compensatory muscle patterns during walking are expected to diminish.

- What are the effects of timing of providing ankle-foot orthoses on the occurrence of falls and fall related events in acute stroke patients in a rehabilitation setting?

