### 3. STUDY DESIGN

In this explorative study a randomised experimental longitudinal design will be used. The intervention concerns the timing of providing AFOs to acute stroke patients during the rehabilitation process. In two groups the effect of timing of providing AFOs will be compared: 1) providing an AFO within one week after admission in the rehabilitation centre ( $\pm$  2 weeks after stroke); and 2) providing an AFO 8 weeks later.

Acute stroke subjects with indication for using an AFO during rehabilitation will be included. To avoid differences in therapy treatment and intensity between subjects, only one rehabilitation centre will participate in this study; The Roessingh Rehabilitation Centre in Enschede. Patients will be included in the study as soon as possible after admission into the Roessingh. In daily practice, this is within approximately 14 days after stroke onset. Participating patients will be randomised into 2 groups. The first group will receive the AFO within one week after admission into the Roessingh (referred to as the “early” AFO group). Subjects in the “early” group can practise walking and transferring using the AFO all day long: during the physiotherapy sessions, during other therapy sessions and during the stay at the ward. The second group (referred to as the “late” AFO group) will receive the AFO 8 weeks later than the “early” AFO group, approximately 10 weeks after stroke. In the period before receiving the AFO, this group will practise walking and transferring without support of the ankle and foot. If, during physiotherapy sessions, practising without support of the ankle appears to be impossible, bandaging of the ankle and foot is allowed, but only during the physiotherapy sessions. This bandaging is not continued during other therapy sessions, or during the stay at the ward.

The “late” AFO group will receive the AFO approximately 10 weeks after stroke. This period is chosen for 2 reasons. First, this is comparable to the period in which in clinical practice the final AFO is usually provided according to physiotherapists at the Roessingh (approximately 8-12 weeks after stroke). Second, prospective stroke studies indicate that the process of spontaneous recovery after stroke is almost completed after approximately 6-10 weeks (Buurke et al. 2008; Kwakkel et al. 2006).

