### 4.2 Inclusion criteria

- admission into the Roessingh Rehabilitation Centre
- unilateral ischaemic or haemorrhagic hemiparetic stroke (single and first ever or history of previous stroke with full physical recovery)
- time since stroke max 6 weeks
- age 18 years or older
- indication to use an AFO during rehabilitation because of:
  - problems with stability in stance
  - problems with footclearance during swing
  - problems with foot prepositioning in early stance
- no severe deficits in communication
- no severe deficits in memory and understanding

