### Gait analysis

Gait analysis will be performed at the RRD. Both groups will be measured five times (see table 1):

- T1: The first measurement will be performed at the end of the first week of the study (T1). Subjects in the “early” AFO group receive their AFO at the beginning of this week and are measured with and without AFO. Subjects in the “late” AFO group will be measured without AFO.
- T9: The second gait analysis will be performed in week 9 of the study (T9). Subjects in the “early” group are now using the AFO for 8 weeks, subjects in the “late” group receive their AFO in this week. From now on both groups will be measured with and without using the AFO.
- T17: The third gait analysis will be performed in week 17 of the study (T17). Subjects in the “early” group are using their AFO for 16 weeks, subjects in the “late” group are using their AFO 8 weeks.
- T26: The fourth gait analysis will be performed in week 26 of the study, approximately 6 months after stroke.
- T52: The last measurement will be performed 1 year after stroke.

Measurements will be performed while walking at comfortable speed. If necessary, subjects can use walking aids (e.g. canes). The movements of the body while walking will be recorded with a VICON video based 3D kinematic measurement system (VICON-MX13+, Vicon Oxford Metrics, Oxford, UK), consisting of 6 infrared cameras, using passive reflexive markers. Subjects are asked to put on a short and top so the skin is suitable for proper marker placement. These markers will be attached to the subject on the feet, lateral malleolus, tibia, knee and femur of both legs, as well as on the pelvis. Vertical ground reaction forces will be measured with force plates, covered in the level walkway (AMTI-OR6-5, Advanced Medical Technologies, Inc, Massachusetts, USA). During the gait analysis muscle activity will be recorded using surface EMG from several superficial muscles of both legs using wet-gel silver/silver-chloride electrodes. Signals will be collected from the m. Rectus Femoris, m. Vastus Lateralis, m. Semitendinosus, m. Gastrocnemius and m. Tibialis Anterior. Electrode placement, skin preparation and related issues are performed according to the guidelines presented by SENIAM (Hermens et al. 1999).

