| T1                                   | Modified Nottingham Sensory Ass
Mini-Mental State Examination
Utrecht Communicatie Onderzoek                                                                                                                                                             | proprioception and sensation
cognition
communication                                                                                                                             | *
**
***                                |
| T1, T9, T17, T26, T52                | Clinical Gait analysis
Mappam test
Modified Ashworth Scale
Brunnstrom Fugl Meyer (leg portion)
Passive ankle range
Barthel Index
Nottingham Extended ADL (T26/52)
Stroke Impact Scale                                                     | joint angles/EMG/GRF
stretch reflex, instrumented
resistance to passive
motion
synergies
passive range of motion
ADL
extended ADL
quality of life after stroke | *
*
*
*
*
**
**
**       |
| T1-T18: 2-week interval,
T26, T52 | Motricity Index (leg portion)
10-m walking test
6-min walking test
Berg Balance Scale
Timed Up and Go test
Stairtest
Rivermead Mobility Index
Functional Ambulation Categories
therapist- and subject questionnaires
(attachment 1) | muscle control and strength
walking speed
walking endurance
balance
mobility
mobility
mobility
independence in walking
treatment and falls                     | *
*
*
*
*
*
**
***
** |
| T1-T26: every month,
T52          | Falls Efficacy Scale
subject questionnaire (attachment 2)                                                                                                                                                                                                   | fear of falling
pain and AFO/shoe use                                                                                                                                               | **
**                                      |

*T1 = week of inclusion and providing AFO to the “early” group;*

*T9 = week of providing AFO to the “late” group;*

*T26 = 6 months after stroke*

*T52 = 12 months after stroke*

*\*) physical test; \*\*) questionnaire; \*\*\*) rating scale*

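### T26 is defined both as study week 26 and as 6 months after stroke; the two differ by about 5 weeks for a patient entered at the 6-week eligibility limit, which also does not fit the stated 2-versus-10-week timing

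*Protocol*

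**What the plan says.** T1, T9 and T17 are counted in study weeks from inclusion (section 6.3, Gait analysis; Table 1 footnote). T26 is anchored twice:

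- Section 6.3, Gait analysis: "The fourth gait analysis will be performed in week 26 of the study, approximately 6 months after stroke".
- Section 6.3, Clinical tests, places T26 and T52 at 6 and 12 months after stroke, and the Table 1 footnote repeats it: "T26 = 6 months after stroke". Table 1 lists the gait analysis under this same T26 label.

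T52 has one anchor wherever it appears. The gait analysis text has "The last measurement will be performed 1 year after stroke", and section 3, the clinical-test text and Table 1 agree.

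On entry, section 4.2 admits patients with "time since stroke max 6 weeks". Section 3 describes inclusion soon after admission: "In daily practice, this is within approximately 14 days after stroke onset". It says the late group "will receive the AFO 8 weeks later than the “early” AFO group, approximately 10 weeks after stroke". It supports that time point by usual practice (8 to 12 weeks after stroke) and by studies in which "spontaneous recovery after stroke is almost completed after approximately 6-10 weeks". The hypothesis on walking impairments in section 2 also speaks of about 2 and about 10 weeks after stroke. The intervention itself (Summary, sections 3 and 5.1) is defined from admission: provision in the first week, or 8 weeks later.

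**The concern.** A visit label should fix when a measurement is taken. Here T26 follows the study clock in one place and the stroke clock in two others, and the clocks separate as entry gets later. Section 6.1.2 says that gait analysis is there to explain changes at the activity level, which requires the gait data and the clinical tests at T26 to describe the patient at the same time. T26 also carries a main outcome measured only there and at T52, the Nottingham Extended ADL index (Table 1).

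The second part is interpretive. If the report says that AFOs at about 2 weeks were compared with AFOs at about 10 weeks after stroke, that describes a patient entered at 2 weeks. It does not describe one entered near the permitted limit.

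**Working it through.** This is calendar arithmetic. Inputs: usual entry about 2 weeks after stroke (section 3); maximum 6 weeks (section 4.2); an 8-week delay (sections 3 and 5.1); T1 is the week of inclusion (Table 1). Assumption: the 6-week limit applies at inclusion. Let s be weeks since stroke at the start of study week 1, and take 6 months as 26 weeks and 12 months as 52 weeks.

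**The plan's own figure.** Late provision is at s + 8. At s = 2 this is 10 weeks after stroke, as stated.

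**Formulas.**
- Study week k starts s + k − 1 weeks after stroke, so study week 26 starts at s + 25.
- Gap between the two T26 rules: (s + 25) − 26 = s − 1 weeks, plus up to 1 week if the visit falls at the end of study week 26.
- If T26 is 26 weeks after stroke, AFO use by then is 26 − s weeks (early group) and 26 − (s + 8) = 18 − s weeks (late group).
- At T52 on the stroke clock, AFO use is 52 − s and 44 − s weeks.

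| s (weeks) | Late AFO, weeks after stroke | Start of study week 26, weeks after stroke | Gap between T26 rules | AFO use at T26 on stroke clock, early / late | AFO use at T52, early / late |
|---|---|---|---|---|---|
| 2 | 10 | 27 | 1 | 24 / 16 | 50 / 42 |
| 4 | 12 | 29 | 3 | 22 / 14 | 48 / 40 |
| 6 | 14 | 31 | 5 | 20 / 12 | 46 / 38 |

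**Reading the table.**
- At s = 6 the stroke-clock T26 falls at the start of study week 27 − 6 = 21, which is 4 weeks after T17. The study-clock T26 falls 26 − 17 = 9 weeks after T17.
- Between patients entered at 2 and 6 weeks the spread is 4 weeks whichever clock is used. On the study clock it is in time since stroke (27 to 31 weeks). On the stroke clock it is in AFO use (24 to 20 weeks early, 16 to 12 weeks late).
- At T52 time since stroke does not vary, and AFO use varies by 4 weeks.
- Early minus late AFO use is 8 weeks in every row.
- At s = 6, provision is at about 6 versus 14 weeks after stroke. The late time lies outside the 8 to 12 weeks given as usual practice, and the early time is already at the start of the 6 to 10 week period cited for recovery.

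**The case against.** The weeks are marked as approximate, the 2-week entry is described as usual practice, and the 6-week figure is only an outer limit. At s = 2, study week 26 covers weeks 27 to 28 after stroke, or 6.2 to 6.4 months, which approximately 6 months can absorb. The primary objective and its hypothesis name no weeks after stroke, and the intervention is defined from admission. All of this stands. It makes the mismatch between eligibility and the stated timings a matter for reconciliation rather than a flat contradiction. It does not rescue T26, because an approximation that covers 1 week does not cover 5.

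The objection is also right against three stronger readings that a reader might infer:

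- *T52 is affected in the same way.* It is not. It is 12 months after stroke throughout, and moving it to the study clock would create a spread in time since stroke that is now absent.
- *Patients differ by 5 weeks at the same visit.* From the documents' own 2 and 6 weeks the spread is 4. A spread of 5 needs an assumed entry at 1 week. Five weeks is the gap between the two T26 rules for one patient entered at 6 weeks.
- *The comparison between groups is biased.* Allocation is randomised (section 6.2), both arms follow the same schedule, and nothing suggests that the clock would be chosen differently by arm.

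Finally, covariate adjustment is often left to a statistical analysis plan, which is not available here. Its absence from section 8.2 is therefore not a fault, and it is offered as an improvement.

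**Conclusion.** The point holds in limited form. T26 has two definitions that cannot both be met for a patient entered late: about 1 week apart at s = 2 and about 5 weeks at s = 6. The eligibility limit also allows provision at about 6 versus 14 weeks after stroke, which does not fit the approximate 2 versus 10.

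The consequence is extra variability at T26, a weaker link between gait and activity findings for late entrants, and uncertainty about which time after stroke the result applies to. The effect on variance or power cannot be quantified, because the protocol gives no distribution of entry times. If nearly everyone enters at about 2 weeks, the practical effect is small. The randomised contrast, an 8-week delay, is unaffected.

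**What to change.** 1. Give T26 one anchor in section 6.3 (both the gait analysis and clinical test text) and in the Table 1 footnote, so that all T26 measurements belong to one visit. The sponsor should choose the clock knowing the trade-off: the stroke clock equalises time since stroke, and the study clock equalises duration of AFO use. Leave T52 at 12 months after stroke.
2. For the main between-group comparisons, replace the unadjusted t-test named in section 8.2 with a comparison adjusted for weeks since stroke at inclusion, using a model suited to each outcome. Section 6.1.3 already collects this variable. Once T26 has one clock, whatever that clock does not hold constant is a straight-line function of s, so the covariate takes up its linear part.
3. Describe the tested contrast throughout as an 8-week delay in AFO provision, and report actual weeks after stroke at provision by group.
4. The sponsor must reconcile the section 2 hypothesis, the section 3 timings and the section 4.2 limit. No limit or timing is proposed here.

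The cost is wording in a few places, one model parameter, and reporting from data already planned or readily recorded. No extra visit or patient is needed.

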## **6.4 Withdrawal of individual subjects**

Subjects can leave the study at any time for any reason if they wish to do so without any consequences. The investigator can decide to withdraw a subject from the study for urgent medical reasons.

### **6.4.1 Specific criteria for withdrawal**

Subjects will be withdrawn when either the subject him/herself or the researcher indicates that the load of the measurements is too much.

## **6.5 Replacement of individual subjects after withdrawal**

Individuals withdrawn from the study will be replaced by new subjects using “modified intention to treat analysis” in case individuals are withdrawn before start of the intervention (using an AFO).

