### *New research*

In order to study the effects of timing of providing AFOs in stroke patients a new longitudinal research is proposed. In this study acute stroke patient will be included and 2 intervention groups will be arranged. Both intervention groups differ in the moment in which the AFO will be provided during the rehabilitation process. One intervention group will receive an AFO within one week after admission into the rehabilitation centre. Subjects in the other intervention group will receive an AFO 8 weeks later.

The rationale behind the early provision of AFOs is that AFOs are reported to improve a safe walking pattern, for example in case of a foot drop (Geboers et al. 2002). In a recent study stroke patients felt that walking devices (including AFOs) improved their walking, confidence and safety (Tyson and Rogerson, 2009). If patients are able to ambulate at a safer level earlier in the rehabilitation phase due to early prescription of AFOs, patients may become more active while experiencing less falls. This might stimulate rehabilitation, as patients may become more independent in activities of daily life (ADL) in an earlier phase of the rehabilitation, or reach a higher level of ADL-independence at the end of rehabilitation. Other positive effects of early AFO use might be seen on the level of compensation strategies. In case of a dropfoot due to paresis of the m. Tibialis anterior, compensatory circumduction of the hip is often seen in swing phase to overcome the relative long leg length. If AFOs are provided earlier in rehabilitation, those compensatory movements might not be necessary and possibly walking patterns and walking speed will improve.

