## 5. TREATMENT OF SUBJECTS

### 5.1 Investigational product/treatment

Acute stroke patients with indication for using an AFO will be included in this study. The intervention of interest is the timing of providing an AFO during the rehabilitation process. Early provision of AFOs (within one week after admission into the rehabilitation centre), will be compared with providing an AFO 8 weeks later.

There are several types of AFOs that are used in daily practice. Three commonly used types of AFOs are selected for this study (see pictures below). With the selected types of AFOs both patients with problems during the swing and stance phase of walking can be provided with an AFO. The so called “Dynafo” and “Ottobock” orthoses are flexible types of orthoses. They allow some dorsiflexion and vertical rotation movement in the ankle and are primarily used to correct a dropfoot and small varus deformities of the ankle and foot during the swing phase of walking. In case a higher degree of stability is needed, for example to counteract hyperextension of the knee in stance, or to correct varus deformity at the ankle in stance and/or swing due to spasticity, the “Camp” orthosis will be used. This is a more rigid type of AFO, which surrounds most of the calf and both malleoli, and therefore restricts most movement in the ankle. All AFOs are fixed with a band around the lower leg and are worn inside the shoe with a sole plate that extends below the foot. The selected AFOs can be provided for the left or right lower limb and are fabricated in various sizes. If necessary, for example in case of sensation disorders, the sole plate will be customized.

[figure not shown]

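### Section 6.5 replaces subjects who withdraw before first using an AFO, a window of at most one week in the early arm but about eight weeks in the late arm, so the analysis set depends on allocation

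*Protocol*

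**What the plan says.** Section 6.5 reads "Individuals withdrawn from the study will be replaced by new subjects using" a modified intention-to-treat analysis, "in case individuals are withdrawn before start of the intervention (using an AFO". The bracket makes first AFO use the trigger in both arms.

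The arms reach that point at different times by design. Section 3 says of the early arm: "The first group will receive the AFO within one week after admission into the Roessingh". The gait-analysis part of section 6.3 puts it at the start of study week 1: the early "AFO group receive their AFO at the beginning of this week and are measured with and without AFO". The late arm, in section 3, "will receive the AFO 8 weeks later than the" early arm; the flowchart legend and Table 1 call that week T9.

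Section 5.1 describes what is being tested: "The intervention of interest is the timing of providing an AFO during the rehabilitation process". Section 3 also sets out what late-arm subjects do while waiting: they practise without ankle support, with bandaging allowed only in physiotherapy sessions.

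Four other provisions bear on the point. Patients and assessors are not blinded (6.2). Subjects may leave at will or be withdrawn for urgent medical reasons (6.4). Subject or researcher may trigger withdrawal because the measurement load is too great (6.4.1). Nobody is followed after withdrawal (6.6).

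**The concern.** A modified intention-to-treat set is usually defensible when the exclusion cannot depend on the arm, for instance when it covers only a short period common to both arms before treatment. Here the exclusion period is part of what was randomised. The AFO-free wait is the late arm's assigned strategy, yet section 6.5 treats a late-arm subject in week 6 as someone who has not started.

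So a post-randomisation event, occurring with the arm known, decides analysis membership differently in the two arms, and replacement acts almost entirely on one side. T1 to T9 is also the only stretch in which the arms are meant to differ in AFO use. The section 2 hypothesis that early provision reduces falls depends heavily on those weeks. Therapist and subject questionnaires covering falls run two-weekly from T1 (Table 1), so a late-arm subject who leaves in week 6 may already have contributed relevant records that the rule could remove.

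**Working it through.** **1. The plan's own figure.** Section 4.4 gives about 20 subjects a year for 30 months: 20 × 30/12 = 50, which reproduces. With two arms and blocks of 4, and assuming 1:1 allocation, that is about 25 per arm. Section 4.4 gives no withdrawal rate.

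**2. The same withdrawal in week 5, side by side.**

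| | Early arm | Late arm |
|---|---|---|
| AFO already used? | Yes, since week 1 | No, due at T9 |
| Replaceable under 6.5? | No | Yes |
| In the analysis set? | Yes | No, on the natural reading of modified |
| Data from T1 to week 5 | Kept | May be lost |
| Data from T9 onward | Missing (6.6) | Missing (6.6) |

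The arms are treated differently in every row but the last.

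**3. Expected removals.** Assume the same weekly withdrawal risk h in both arms. The share withdrawn before first AFO use is q = 1 − (1 − h)^w, with w = 1 week (early) and w = 8 weeks (late), or 9 if counted to the end of week T9. Expected removals are 25q. The values of h are assumptions.

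| h per week | Early, w = 1 | Late, w = 8 | Late, w = 9 | Ratio, 8 weeks to 1 |
|---|---|---|---|---|
| 0.5% | 0.5%, 0.13 of 25 | 3.9%, 0.98 of 25 | 4.4%, 1.10 of 25 | 7.9 |
| 1% | 1.0%, 0.25 of 25 | 7.7%, 1.93 of 25 | 8.6%, 2.16 of 25 | 7.7 |
| 2% | 2.0%, 0.50 of 25 | 14.9%, 3.73 of 25 | 16.6%, 4.16 of 25 | 7.5 |

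For example, at 1%: 1 − 0.99^8 = 0.0773, and 25 × 0.0773 = 1.93.

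The chance that at least one of 25 is removed is 1 − (1 − q)^25. Early against late (8 weeks), it is 12% against 63%, 22% against 87%, and 40% against 98% at the three rates.

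**4. A milder assumption.** Spread a total withdrawal T evenly over 52 weeks: weekly hazard −ln(1 − T)/52, share 1 − exp(−hazard × w). For T of 10%, 20% and 30%, the late arm loses 0.40, 0.84 and 1.33 of 25 in eight weeks; the early arm loses 0.05, 0.11 and 0.17 in one week. The counts are smaller, but the ratio remains close to eight to one.

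**5. Bias.** Turning these counts into a shift in outcome needs three things the protocol does not give: how many leave, how leavers differ from stayers, and whether they differ by arm. No bias in SD units and no type I error follows from the document.

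**The case against.** The strongest objection is section 6.6. A reader might infer that the trial compares all early-arm subjects with only those late-arm subjects who lasted eight weeks, and might simulate a biased difference with an inflated type I error from that. The protocol does not support this. Follow-up ends at withdrawal in both arms, so an early-arm subject who leaves in week 5 also has no T9, T17, T26 or T52 data. If the same kinds of subjects leave both arms at the same rate and only observed data are compared, the selection is the same on both sides and the expected difference in later outcomes is zero. This objection stands. It confines the damage specific to 6.5 to data gathered before withdrawal, to leaving that differs by arm, and to one-sided replacement.

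A reader might also infer that late-arm subjects who recover too well to need an AFO are dropped, which would favour early provision. Section 6.5 is triggered by withdrawal from the study, not by never using an AFO, and 6.4 and 6.4.1 do not name good recovery as a ground. A late-arm subject who stays in without an AFO is not covered. Measurement load and medical reasons could as easily remove poorer recoverers, which would flatter the late arm.

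Third, the text says replaced, not deleted; adverse events are all recorded (7.2); and a statistical analysis plan may define the analysis sets. That is fair, and exclusion is an inference. But if replaced subjects stayed in the analysis, modified would have no evident meaning, and a plan that followed 6.5 would inherit its trigger.

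Finally, the study calls itself explorative. That lowers the stakes but does not make an arm-dependent analysis set acceptable in a randomised comparison.

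**Conclusion.** The point holds as a fault in a rule the protocol states. Section 6.5 ties replacement, and by natural reading exclusion, to an event that the design places about eight weeks apart in the two arms, and it conflicts with section 5.1 on when the intervention begins. Membership of the analysis set therefore depends on allocation after unblinded randomisation, and late-arm data from the wait, falls among them, can leave the comparison.

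Under equal weekly risks of 0.5% to 2%, about 1 to 3.7 late-arm subjects of 25 would be removed, against 0.1 to 0.5 in the early arm. If withdrawal is rarer, as in the 10% to 30% per year case, the late arm loses roughly 0.4 to 1.3. These counts rest on assumed rates, equal risk in both arms and 1:1 allocation. The size and direction of any resulting bias are unknown, and the effect may be small if few leave early. A larger sample would not remove the asymmetry.

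**What to change.** Reword section 6.5 so that every randomised subject is analysed in the allocated arm from T1, whether or not an AFO was ever used, and all data collected before withdrawal, including falls and adverse events, are kept. Permit replacement only for subjects who withdraw before their allocation is disclosed, which gives both arms the same window, or treat it as extra recruitment that removes nobody.

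Change section 6.6 with it: where the subject consents, remaining outcomes are sought after withdrawal, in the same way in both arms. Without this, subjects retained under the new 6.5 would still have nothing recorded after they leave.

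The cost is two short sections of text, some follow-up effort, and an analysis in which some subjects have incomplete outcomes that must be handled.
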